### Measurement

#### Baseline measurement

The implant stability will be monitored by means of resonance frequency analysis (Osstell mentor; Integration Diagnostics AB, Göteborg, Sweden) immediately after surgery. After the implant placement, the implant stability will be tested by the Osstell Mentor in four directions (buccal, palatal, mesial, and distal). If the implant is deemed unable to maintain initial stability, the patient will be excluded from the current trial. The peri-apical radiographs and cone beam CT examination will be taken after the surgery. These digital radiographic data will be used as the baseline radiographic data.

### Examination during the follow-ups

#### Follow-up plan

All patients will be recalled for a follow-up session at weeks 2, 6, 8, 12, 16, 26, and 52 after the surgery. For each session, the implant and its supra-structure and mucosa around the implant will be examined. The implant stability will be examined at weeks 6 8, 12, 16, and 26 after the surgery. For weeks 26 and 52 after the surgery, the peri-apical radiographic examinations will be performed to record the hard tissue and bone substitute alterations around the implant. For standardization, the paralleling technique with a rinnfilm holder (XCP Instruments; Rinn Corporation, Elgin, IL, USA) will be applied. Surgical complications, which include infection, hematoma, nasal bleeding, nasal obstruction, and benign paroxysmal positional vertigo (BPPV), will be documented. Any complications of implant and its supra-structure will be documented. Besides, patients will finish a VAS scale to evaluate pain, swelling, and bleeding during the first two weeks after surgery.

### Primary parameters of the trial

The primary parameters of the current trial are implant survival rate, implant stability, and the bone remodeling around the implant.

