### Sample size

The sample size of the current trial is calculated based on the formula: *n* = 2(t_α_ + t_1-β_)^2^σ^2^/δ^2^. According to the preliminary experiment results and data analysis from currently published articles, the difference of the bone remodeling with and without bone grafting groups (δ) is around 0.8 mm, the difference of the bone remodeling between the original TSFE groups and modified TSFE groups is around 0.5 mm, and the standard deviation in groups (σ) is around 1 mm.

Thus, if the inspection level (α) is set at 0.05 and the power of test (β) is set at 90%, then 27 participants will be required for each group. Given a loss to follow-up rate of around 10%, the study would be anticipated to require 30 participants for each group. As a result, this trial will require at least 120 participants in its current setup.

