### Statistical analysis

For any continuous data (such as residual bone height or marginal bone remodeling), the inter-examiner agreement between the two examiners will be tested by the intra-class correlation coefficient. For the descriptive data, the inter-examiner agreement will be tested by the Cohen’s κ statistics.

The descriptive data will be expressed in absolute or relative percentage forms, and differences between the two subgroups will be analyzed by chi-squared test. The continuous data will be represented by mean and standard deviations, and the difference between the groups will be tested by analysis of variance (ANOVA).

In order to avoid the interference of measurement metrics due to having two main factors (surgical methods and bone grafting) in the current study, groups that are identical on individual aspects will be combined to discover the influence on the primary results by surgical method and bone grafting, respectively. For the surgical methods, results will be compared between the combined groups 1 + 2 and 3 + 4, whereas for the bone grafting, results will be compared between the combined groups 1 + 3 and 2 + 4. The difference between the groups will be tested by unpaired *t* test.

The statistical significance difference will be set as a *P* value of less than 0.05. All data analyses will be performed by SPSS statistical software .

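### Three unranked primary outcomes are each tested for two factors at an unadjusted 0.05, so the chance of at least one false primary finding is about 18–26%, not 5%

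*Protocol article*

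**What the plan says.** All places are in the protocol article.

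- **Primary parameters of the trial:** "The primary parameters of the current trial are implant survival rate, implant stability, and the bone remodeling around the implant". The section gives no order, no visit and no rule on how many of the three must succeed.
- **Statistical analysis, aim of pooling the arms:** groups that share a factor level are combined "to discover the influence on the primary results by surgical method and bone grafting, respectively".
- **Statistical analysis, the two contrasts:** "For the surgical methods, results will be compared between the combined groups 1 + 2 and 3 + 4", and "for the bone grafting, results will be compared between the combined groups 1 + 3 and 2 + 4".
- **Statistical analysis, threshold:** a single criterion, a P "value of less than 0.05", applies to everything. It is not split or ordered.
- **Sample size:** the inputs are differences in bone remodeling only: 0.8 mm for "the difference of the bone remodeling with and without bone grafting groups", 0.5 mm between the two techniques, and a standard deviation of 1 mm. Survival and stability do not enter.
- **Follow-up plan:** "The implant stability will be examined at weeks 6 8, 12, 16, and 26 after the surgery". A further reading is taken straight after surgery (Baseline measurement). Follow-up radiographs are planned at weeks 26 and 52. No visit is named as decisive.

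**The concern.** When several outcomes share the primary label, with no ranking and no joint rule, a significant result on any of them can be reported as the trial's primary finding. Testing each for two factors doubles the opportunities. The 0.05 threshold then describes a single test and not the trial's conclusion. A reader of the results paper could not tell a planned headline result from the most favourable of six. Only one of the three outcomes has a sample size behind it, so equal primary status also gives survival and stability a standing that the design does not support.

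**Working it through.** **1. Reproduce the plan's own figure.** The Sample size section uses n = 2(t_α + t_1−β)²σ²/δ². With normal quantiles, δ = 0.8, σ = 1 and 90% power:

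- one-sided 0.05: 2 × (1.645 + 1.282)² / 0.64 = 26.76, rounded up to 27 per arm. This matches the plan.
- two-sided 0.05: 2 × (1.960 + 1.282)² / 0.64 = 32.84, rounded up to 33 per arm. This does not match.

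Then 27 / 0.9 = 30 per arm and 4 × 30 = 120, as stated. The figure therefore comes from bone remodeling and the 0.8 mm grafting difference. The sidedness is not stated and is a separate matter. After 10% loss, each pooled comparison has 2 × 27 = 54 per side.

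**2. Count the primary tests.** 3 outcomes × 2 factors = 6. This counts each outcome once. It leaves out repeat visits and the four-group ANOVA that the same section also mentions.

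**3. Chance of at least one false positive if the tests are independent.**

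- six tests: 1 − 0.95⁶ = 26.5% (Bonferroni ceiling 6 × 0.05 = 30%)
- one factor alone, three tests: 1 − 0.95³ = 14.3%

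**4. Allow for dependence.** Outcomes on the same implant are correlated, and a chi-squared test on few failures is conservative. A null simulation of the 2 × 2 design used 27 per arm, t tests for stability and bone remodeling, a Pearson chi-squared test for survival and 8,000 simulated trials per setting. Survival (95% or 98%) and the correlation between outcomes (0 to 0.8) are assumptions; the documents give neither.

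| Assumed survival | Any of six tests | Any of three, one factor | Actual size of one survival test |
|---|---|---|---|
| 95% | 21.4–25.1% | 11.0–13.7% | about 4.4% |
| 98% | 17.9–21.2% | 9.4–11.1% | about 1.5% |

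**5. Lower limit set by the two factors.** With equal arms the two contrasts are orthogonal. Even if the continuous outcomes were perfectly correlated, two independent tests would remain: 1 − 0.95² = 9.75%.

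**6. Power for a single primary outcome, 54 vs 54, σ = 1.** Power = Φ(δ / √(2/54) − z), two-sided, with √(2/54) = 0.1925.

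| Difference | Each factor at 0.05 (z = 1.960) | Each factor at 0.025 (z = 2.241) |
|---|---|---|
| 0.8 mm | Φ(4.157 − 1.960) = 98.6% | Φ(4.157 − 2.241) = 97.2% |
| 0.5 mm | Φ(2.598 − 1.960) = 73.8% | Φ(2.598 − 2.241) = 63.9% |

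**The case against.** **The factors are two questions, not one family.** Objectives and hypotheses numbers them separately, and many factorial trials give each factor its own 5%. This stands as a legitimate choice. It reduces the excess to at most 14.3% per factor, or about 9–14% in the simulation, but does not remove it. The plan would have to state the choice. The same standard must also apply to the remedy: one outcome tested at 0.05 for each factor still gives 9.75% across both if they are counted as one family.

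**An article condenses, and a statistical analysis plan may exist.** This is fair for visit-level models and testing order. It does not cover what the article affirmatively states, which is three equal primary outcomes and a flat threshold.

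**A joint rule may be intended.** If all three outcomes had to succeed, there would be no inflation. No such rule appears.

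**The hypotheses speak of similar results.** The planned tests are for difference. That mismatch is a separate issue and leaves the multiplicity in place.

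**Stronger readings that the documents do not support.**

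- A reader might infer that every stability and radiograph visit is tested separately, which would push the error rate well beyond 26%. The article describes repeated measurement and names no decisive visit, but it does not say each visit is tested. Any further inflation is conditional, and no figure for it is used here.
- A reader might conclude that survival has a specific, very low power. The documents give no expected survival rates, so any such figure would depend on assumed rates. The point that holds is narrower: survival was not sized.
- A reader might take week 52 as the visit the trial was sized on. The Sample size section ties neither difference to a week.

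**Conclusion.** The concern holds in this form. The stated rules give six primary tests at an unadjusted 0.05, with a familywise error of 26.5% under independence and about 18–25% under the correlations and survival rates assumed above. For each factor taken alone it is at most 14.3%. The result assumes that any one significant primary outcome would count as a finding, which the text allows, and that each outcome is tested once per factor. It does not depend on how visits are handled. The defect affects how the headline result can be read. It does not affect the conduct of the trial or the number of patients, and it should be corrected.

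**What to change.** - Name bone remodeling as the single primary outcome, at one pre-specified visit. Week 52, the last planned radiograph, is an example; the plan should say which week its 0.8 mm and 0.5 mm refer to.
- Make implant survival and implant stability secondary.
- Choose one error rule and state it. Either test each factor at 0.025, which holds the error across both at 5% or less, or declare the factors separate questions, each tested at 0.05.

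**Cost.** No extra patients, visits or procedures are needed. Two outcomes lose the primary label. Splitting alpha lowers power for the 0.5 mm technique difference from about 74% to about 64%; for 0.8 mm it stays at about 97%. Keeping all three primaries with Bonferroni (0.05 / 6 = 0.0083 each) costs more: bone remodeling power would be about 94% for 0.8 mm and 48% for 0.5 mm.

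Two cautions apply. The Challenges section warns that the sinus floor border can be hard to recognise on periapical films, so a sole primary outcome based on them depends on careful reading rules. Also, the Timeline section puts the start of recruitment in December 2017, so this is a substantive change. It needs a dated amendment and a registry update before any outcome data are examined.

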### Secondary parameters

The secondary parameters of this study include the following:1. VAS scale to evaluate pain, swelling, or bleeding after the surgery or a combination of these.2. Complications during and after the surgery which including infection, hematoma, nasal bleeding, and BPPV.3. Mucosal condition around the implant: The parameters include depth of probing, sulcus bleeding (by modified sulcus bleeding index), plaque around the restorations (by modified plaque index) will be documented. And the occurrence of biological complications (peri-implantitis and peri-implant mucositis) will be recorded.

### Sample size

The sample size of the current trial is calculated based on the formula: *n* = 2(t_α_ + t_1-β_)^2^σ^2^/δ^2^. According to the preliminary experiment results and data analysis from currently published articles, the difference of the bone remodeling with and without bone grafting groups (δ) is around 0.8 mm, the difference of the bone remodeling between the original TSFE groups and modified TSFE groups is around 0.5 mm, and the standard deviation in groups (σ) is around 1 mm.

Thus, if the inspection level (α) is set at 0.05 and the power of test (β) is set at 90%, then 27 participants will be required for each group. Given a loss to follow-up rate of around 10%, the study would be anticipated to require 30 participants for each group. As a result, this trial will require at least 120 participants in its current setup.

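### The figure of 27 per group rests on the 0.8 mm grafting difference at an unstated one-sided alpha; the planned technique comparison at 0.5 mm has about 73% power two-sided, and below 90% on any reading

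*Protocol article*

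**What the plan says.** The Sample size section gives the formula n = 2(t_α + t_1-β)²σ²/δ² and these inputs:

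- Grafting: "the difference of the bone remodeling with and without bone grafting groups (δ) is around 0.8 mm".
- Technique: "the difference of the bone remodeling between the original TSFE groups and modified TSFE groups is around 0.5 mm".
- Spread: "the standard deviation in groups (σ) is around 1 mm".
- Error rates: "if the inspection level (α) is set at 0.05" and "the power of test (β) is set at 90" percent.

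Its conclusion is "then 27 participants will be required for each group", raised to 30 for roughly 10% loss, hence 120 in four groups. It does not say whether alpha is one-sided or two-sided, or which of the two differences produced 27.

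The Statistical analysis section tests each factor on pooled groups by unpaired t test. For technique, "results will be compared between the combined groups 1 + 2 and 3 + 4"; for grafting, groups 1 + 3 are compared with 2 + 4. The criterion is "The statistical significance difference will be set as a *P* value of less than 0.05", again without sidedness.

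The Objectives and hypotheses section puts technique in the first primary hypothesis. Bone remodeling is one of the three primary parameters.

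**The concern.** Two differences are listed as premises and one sample size is drawn from them, so a reader will take the 90% to cover both factors. A formula with δ squared in the denominator cannot give the same n for 0.8 mm and 0.5 mm: the smaller difference needs (0.8/0.5)² = 2.56 times as many per compared group. If 27 came from 0.8 mm, the technique question has been sized only by whatever pooling happens to supply.

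At stake is how a primary result is read. If technique power is well below 90%, a non-significant comparison says less about a difference of the size the plan itself expects than the Sample size section suggests.

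**Working it through.** **Inputs.** From Sample size: σ = 1 mm; δ = 0.8 mm (grafting) and 0.5 mm (technique); α = 0.05; power 90%; 27 evaluable per group. From Statistical analysis: pooled comparisons, so 2 × 27 = 54 evaluable per side. Normal quantiles: 1.645 (one-sided 5%), 1.960 (two-sided 5%), 1.282 (90% power).

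**Step 1: reproduce 27.** With normal quantiles in the printed formula:

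| δ | One-sided α | Two-sided α |
|---|---|---|
| 0.8 mm | 2(1.645 + 1.282)²/0.64 = 26.8, so 27 | 2(1.960 + 1.282)²/0.64 = 32.8, so 33 |
| 0.5 mm | 2(1.645 + 1.282)²/0.25 = 68.5, so 69 | 2(1.960 + 1.282)²/0.25 = 84.1, so 85 |

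Only the one-sided 0.8 mm cell gives 27. Then 27/0.9 = 30 and 4 × 30 = 120, so the later figures follow. The 0.5 mm difference plays no part in them.

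**Step 2: power of the planned pooled tests.** The standardised distance is δ/(σ√(2/n)).

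- Technique, 54 vs 54: 0.5/√(2/54) = 2.598. Two-sided normal power is Φ(2.598 − 1.960) = 73.8%; one-sided is Φ(2.598 − 1.645) = 83.0%.
- Grafting, 54 vs 54: 0.8/√(2/54) = 4.157. Two-sided normal power is Φ(4.157 − 1.960) = 98.6%.

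Noncentral-t power, which suits a t test, is slightly lower:

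| Comparison | Two-sided | One-sided |
|---|---|---|
| Technique 0.5 mm, 54 vs 54 | 73.1% | 82.6% |
| Technique 0.5 mm, 60 vs 60 (no loss at all) | 77.5% | 86.0% |
| Grafting 0.8 mm, 54 vs 54 | 98.5% | 99.4% |
| Single groups, 0.8 mm, 27 vs 27 | 82.2% | 89.5% |
| Single groups, 0.5 mm, 27 vs 27 | 43.8% | 56.7% |

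**Step 3: effect of the other factor on the pooled t test.** If 1 mm is the SD within each of the four groups, an unadjusted pooled t test leaves the other factor's effect in the error term. For technique, half the pooled patients lie 0.4 mm above and half 0.4 mm below the pooled mean, so the SD becomes √(1 + 0.4²) = 1.077 mm. Two-sided technique power at 54 vs 54 falls to 66.7%. For grafting the SD becomes √(1 + 0.25²) = 1.031 mm, and power stays at 97.9%.

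**Step 4: detectable difference.** At 54 per side, SD 1 mm, two-sided 5% and 90% power, the t test detects 0.63 mm. The normal approximation gives 3.242 × √(2/54) = 0.62 mm.

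**The case against.** The strongest defence is that every printed figure reproduces. The formula shows t_α rather than t_α/2, the symbol δ is attached only to the grafting difference, and with those readings 27, 30 and 120 all follow. That stands: the calculation is not an arithmetic error, and the article nowhere says in so many words that technique has 90% power. But the 0.5 mm difference is listed in the same premise and the conclusion carries no restriction to grafting, so the text leaves a reader to assume that it covers both.

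Sidedness is also open. An unpaired t test can be run either way, and the article does not say which. Two-sided is the usual reading of P < 0.05, but it is an assumption. The technique shortfall does not depend on it: one-sided power is about 83%, and 86% even with no loss.

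Two stronger readings are tempting and are not supported.

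- A reader might infer that all two-sided analyses miss 90%. They do not. The planned grafting test is the pooled one, with about 98% two-sided power. Only a contrast of single groups (27 vs 27) at 0.8 mm drops to 82%, and the article does not name that as its test of the grafting factor.
- A reader might infer that correcting the power figure would guard against reading non-significance as similarity. It would not. A non-significant difference test does not show similarity at 73% or at 90% power. The correction makes the stated property true and does no more.

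**Conclusion.** The point holds for the technique comparison. The sample size was derived from the larger of two stated differences at an unstated one-sided alpha, and the 0.5 mm technique difference was not used. Power for technique is about 73% two-sided, about 67% with the plain pooled t test if the 0.8 mm grafting effect stays in the error term, and about 83% one-sided, against the 90% given. Put differently, the two-sided chance of missing the plan's own expected technique difference is about 27% to 33%, not 10%. The grafting comparison as planned is adequately powered.

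This rests on the article's SD of 1 mm and its two differences, on 27 evaluable in every group, and on two-sided 5% tests where so labelled. The 67% figure further assumes that 1 mm is the within-group SD and that the two effects are additive.

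**What to change.** Keep 120 patients and restate the Sample size section so that it:

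1. says that 27 per group was derived from the 0.8 mm grafting difference at one-sided alpha 0.05;
2. states the sidedness of the planned tests, in agreement with the Statistical analysis section;
3. reports the power of the pooled comparisons with 54 evaluable per side. If two-sided: about 98% for grafting at 0.8 mm; about 73% for technique at 0.5 mm, or about 67% with the unadjusted pooled t test; and 0.63 mm as the difference detectable with 90% power at SD 1 mm;
4. does not present 90% power as applying to the technique question.

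The cost is the rewording of one section and a less favourable stated power for technique. No patients are added. For comparison, 90% two-sided power at 0.5 mm would need 85 evaluable per pooled side, about 43 per group against the 27 planned.

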## Background

When placing implants in the posterior maxilla, the dentist could often face the challenge of insufficient bone volume or poor bone quality or both [1–3]. Some efforts have been made to ensure successful implant treatment in the atrophic posterior maxillae. Sinus floor elevation has been proven to be a predictable surgical procedure to increase the bone height in the posterior maxilla which can be accomplished either through transalveolar sinus floor elevation or through a lateral window technique [4–7]. The transalveolar sinus floor elevation (TSFE) described by Summers in 1994 has been proven to be a predictable surgical procedure to increase bone volume in atrophic maxilla vertically [5, 6]. The original procedure is indicated when the residual volume of alveolar bone is between 4 and 8 mm below the sinus floor and the sinus membrane is elevated with osteotomes of increasing diameter from a crestal approach through the osteotomy prepared for dental implant placement but without need for a lateral window [5, 6].

Compared with the lateral sinus floor elevation (LSFE), the transcrestal sinus floor elevation technique has the advantages of limited trauma, bleeding, and swelling [8]. However, unlike LSFE, the surgical procedure in the TSFE is a visually restrictive technique, which makes it a technique-sensitive procedure, especially when direct visual examination of the sinus membrane is required. Furthermore, the bone height which could be augmented by the osteotomes is limited when compared with the lateral window technique [9].

Some studies reported a relatively high incidence of sinus membrane perforations when TSFE is performed [10]. Thus, some scholars have suggested modifying the operation procedure to reduce the incidence of the membrane perforation and increase the height of the membrane elevation. The methods of hydraulic pressure techniques, crestal non-cutting drills, and piezoelectric equipment have already been introduced to this field and achieved nearly ideal clinical outcomes [11–14].

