### Surgical interventions

For the traditional TSFE, the surgical procedure will be in accordance with the modified Summers’s method which was described by Pjetursson in 2009 [15], and the implant placement procedure will be in accordance with the product description by Straumann AG. The specific procedures are listed as below: the implant bed is prepared with the conventional steps. First, the alveolar ridge will be prepared with the Φ2mm round bur. Then, the Φ2.2 mm pilot drill will be used to ensure the direction and the insertion depth of the implants. The twist drills with Φ2.8 mm, 3.5 mm, and 4.2 mm will be used to enlarge the sockets separately (the diameter of the final drill is determined by the width of the implant). The drills will be stopped at 1–2 mm under the sinus floor. The socket preparation procedures will be irrigated by the 4 °C saline solution to reduce chances ofosteonecrosis which may result from the drill overheating. After that, the Φ2.2 mm osteotome with a concave head will be placed into the socket and the head of the osteotome will be knocked into the sinus cavity about 1 mm. The Φ2.8 mm osteotome then will be placed and knocked in to the sinus just about 1 mm less than the designed length. Finally, the Φ3.5 mm or Φ4.1 mm osteotome will be placed and knocked in to elevate the membrane to the ideal position. Prior to the filling of the bone substitute and implant placement, the sinus membrane will be tested for any perforations by the Valsalva maneuver (nose blowing test). If any air leaked through the implant site, it would have to be assumed that the sinus membrane was perforated; thus, the patient will be dropped from the current study. The patient will receive the appropriate therapy when the membrane is healed.

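### The 10% allowance covers loss to follow-up only, so 30 per group is not expected to leave 27 evaluable patients once perforation and instability exclusions are counted

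*Protocol article*

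**What the plan says.** The Sample size section of the protocol article bases its requirement on bone remodeling in millimetres. For the grafting factor it says that "the difference of the bone remodeling with and without bone grafting groups (δ) is around 0.8 mm", for the surgical method that "the difference of the bone remodeling between the original TSFE groups and modified TSFE groups is around 0.5 mm", and for the spread that "the standard deviation in groups (σ) is around 1 mm". With α of 0.05 and 90% power it arrives at 27 per group, and then continues: "Given a loss to follow-up rate of around 10%, the study would be anticipated to require 30 participants for each group". Four groups of 30 make a minimum of 120. The Missing data section confirms that the sample size estimate took account of loss to follow-up and names no other loss there.

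Two other sections remove patients during or just after surgery:

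- Surgical interventions, when air leaks on the Valsalva test after the osteotome elevation: "it would have to be assumed that the sinus membrane was perforated; thus, the patient will be dropped from the current study". The same test is run in the modified-technique groups, where the consequence is not restated.
- Baseline measurement, after the implant is placed: "If the implant is deemed unable to maintain initial stability, the patient will be excluded from the current trial".

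The Background expects the first of these to occur: "Some studies reported a relatively high incidence of sinus membrane perforations when TSFE is performed". No expected rate, allowance or replacement rule is given for either removal.

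**The concern.** Both removals are triggered by what happens while the assigned technique is being carried out, so they come after assignment. Neither is loss to follow-up. A patient removed in this way gives no bone-remodeling value, and that is the measurement on which the trial was sized. The Missing data section counts dropouts as failures, which can work for implant survival but supplies no value in millimetres.

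Two things are at stake. The number per group on which the power statement rests is not the number the plan can expect to analyse. In addition, the Background presents the modified techniques as a way to reduce perforation, so removals may differ between the methods being compared. The groups could then shrink unequally, and the patients left for analysis would be selected by an outcome of the assigned procedure. The removal rules also sit badly with the intention-to-treat principle invoked under Missing data.

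**Working it through.** **Inputs.** From Sample size: δ = 0.8 mm (grafting) and 0.5 mm (method), σ = 1 mm, α = 0.05 (sidedness not stated), power 90%, loss about 10%, 30 per group. From Statistical analysis: grafting is tested as groups 1 + 3 against 2 + 4, and method as groups 1 + 2 against 3 + 4, by unpaired t test. Assumed, because the documents give no figure: a combined exclusion rate *e* for perforation and instability of 5%, 10% or 20%, equal in all groups.

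**Step 1. Reproduce the plan's figure.** n = 2(z_α + z_power)²σ²/δ².

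- One-sided, 0.8 mm: 2 × (1.645 + 1.282)² / 0.64 = 26.8, so 27. This matches.
- Two-sided, 0.8 mm: 32.8, so 33. This does not match.
- With 0.5 mm: 69 one-sided or 85 two-sided. Neither matches.

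The 27 therefore rests on 0.8 mm, a one-sided 5% level and two single groups. Then 27 / 0.9 = 30, and 4 × 30 = 120.

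**Step 2. Check the reserve.** 30 × 0.9 = 27.0. Nothing remains for any other removal.

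**Step 3. Add the exclusions.** Expected evaluable patients per group = 30 × 0.9 × (1 − e).

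| e | Per group | All four groups | Chance that one group keeps at least 27 of 30 |
|---|---|---|---|
| 0 | 27.0 | 108 | 0.65 |
| 5% | 25.7 | 103 | 0.35 |
| 10% | 24.3 | 97 | 0.15 |
| 20% | 21.6 | 86 | 0.02 |

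The last column is binomial, with 30 patients and retention 0.9 × (1 − e).

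**Step 4. Power at those numbers.** Noncentral t distribution with σ = 1, *m* evaluable patients per side, noncentrality δ/√(2/m) and 2m − 2 degrees of freedom. *m* is the per-group number for single groups and twice that for pooled sides (54 per side at e = 0).

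| e | Two single groups, 0.8 mm, one-sided | Pooled grafting, 0.8 mm, two-sided | Pooled method, 0.5 mm, two-sided |
|---|---|---|---|
| 0 | 0.895 | 0.985 | 0.73 |
| 5% | 0.88 | 0.980 | 0.71 |
| 10% | 0.87 | 0.974 | 0.68 |
| 20% | 0.83 | 0.957 | 0.63 |

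The starting value is 0.895 rather than 0.90 because the plan's formula with normal quantiles is slightly more favourable than the t test.

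**Step 5. Separate the causes.** The pooled method comparison has power of about 0.78 two-sided at the full 60 per side with no losses. The 10% loss takes it to 0.73, and the exclusions lower it from there.

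**The case against.** The strongest reply is that the trial will not test grafting on single groups. It pools them, and the pooled 0.8 mm comparison keeps two-sided power of 0.985 to 0.957 over exclusion rates of 0 to 20%. It falls below 90% only when exclusions reach roughly 37–39% on top of the 10% loss. This stands. A reader might infer that the trial loses its 90% power for grafting, and the documents do not support that.

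A reader might also infer that 27 evaluable patients per group are out of reach. That is too strong as well. The plan speaks of about 10% loss and of at least 120 participants. With 5% loss and 5% exclusions, 30 × 0.95 × 0.95 = 27.1 remain, and even with the full 10% loss and 5% exclusions a given group keeps 27 about one time in three. The shortfall is in the expected number, and its size depends on a rate that the documents do not give.

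Three further points carry weight. Most of the weakness of the 0.5 mm comparison, and the need for an unstated one-sided level to reach 27, are separate defects that exclusions do not cause. Screening for bone density (Exclusion criteria, item 5) and the preoperative cone beam CT should prevent some stability failures. Perforation is described only as relatively frequent in some studies, so nothing in the document supports the upper end of the assumed range.

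None of this restores the per-group figure. The section states its requirement per group, the Statistical analysis section also plans an analysis of variance between groups, and the reserve is still fully used by loss to follow-up.

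**Conclusion.** The point holds in a limited form. The arithmetic from 27 to 30 to 120 is correct for what it covers, but it leaves out two removals that the protocol itself prescribes, so 27 evaluable patients per group is not the expected yield.

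On the basis that produced 27, the cost in power is modest: about 0.01 to 0.03 at 5–10% exclusions, and about 0.07 at 20%. The pooled grafting comparison is not endangered. The pooled method comparison, which bears on the first primary hypothesis, is already short at 0.73 and loses a further 0.02 to 0.10.

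These sizes rest on the assumed rates, on 10% loss, on σ = 1 mm and on equal exclusion across groups. If exclusion differs by technique, the selection of analysed patients matters more than the lost power. The documents give no figure from which to size that effect.

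**What to change.** In Sample size:

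- State that 120 is the number randomised.
- Next to the 10% loss, add an explicit assumed rate or range for exclusions due to perforation and lack of initial stability, with its source. The section cites a preliminary experiment for bone remodeling, but nothing shows that it recorded these rates, so a range may be all that can be given.
- Restate the expected evaluable number (for example, about 24 per group at 10% exclusions) and the power of each planned comparison at 120 randomised, naming the sidedness of the test.

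In Surgical interventions, Baseline measurement and Missing data, reconcile the removal rules with the intention-to-treat statement. Removed patients should stay, in their assigned groups, in the denominators for implant survival and complications, and their number should be reported by group. This concerns the analysis only and leaves the clinical handling of these patients as it is.

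The cost is a slightly less favourable stated power and slightly more analysis work. The trial need not be enlarged, and no procedure is added.
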